**Fig. 1 Fig1:**
[figure not shown]
Timeline for substance administration and MRI protocol for each experimental group at visit 3 and visit 4

At visit 3 and visit 4, blood samples are taken 30 min pre-dose, and 1 h, 3.5 to 4 h, and 4.5 to 5 h after oral drug administration to assess the pharmacokinetics of amisulpride. On visit 4, after the MRI measurements, a physical examination, as well as 12-lead ECG, hematology, chemistry, and coagulation, is performed. A description and a detailed schedule of assessments can be found in Table 1, including questionnaires, laboratory tests, MRI, and the behavioral paradigm.

All assessments are performed by trained professionals in a standardized manner. In order to ensure high-quality standards of the assessments, a common digital manual as well as quality monitoring procedures are implemented (see the “Data management and monitoring” section).

This study was designed by the MSB Medical School Berlin (LC, DW, MSM, SG) and Boehringer Ingelheim Pharma GmbH & Co. KG (MP, GL, SDS, AW). The Charité Research Organisation (CK, RH), a contract research organization and subsidiary of the Charité – Universitätsmedizin Berlin, is responsible for the implementation and, together with the MSB Medical School Berlin, conduction of the trial. SG (MSB Medical School Berlin) is the grant holder and sponsor. SBGneuro Ltd (CB) is responsible for the statistical analysis plan including power analysis. For the interpretation of the data, the responsibility lies with the researchers of the MSB Medical School Berlin. Study organization, recruitment of participants, and monitoring are performed by the Charité Research Organisation (CK, RH). This study is conducted in compliance with Good Clinical Practices (ICH-GCP) and the Declaration of Helsinki. A clinical trial registration is available on ClinicalTrials.gov (NCT number: NCT05347199). The trial is funded by Boehringer Ingelheim Pharma GmbH & Co. KG and approved by the respective local ethics committee (Landesamt für Gesundheit und Soziales, Geschäftsstelle der Ethik-Kommission des Landes Berlin, Berlin, Germany; reference number: 22/029 – IV E 11) and the Bundesinstitut für Arzneimittel und Medizinprodukte, Bonn, Germany.

The reporting of this study protocol was performed according to the Standard Protocol Items Recommendations for Interventional trials (SPIRIT; [44]).

### Eligibility criteria

The main inclusion criteria for all subjects are.Male or femaleAged 18 to 45 years

The main exclusion criteria for all subjects are:Contraindications to MRI conductionContraindication to amisulpride intake according to label informationQT prolongation in ECGA positive SARS-CoV-2 test.Having received prescribed medication within 14 days prior to visit 3 (apart from the contraceptive pill)

The main inclusion criteria for the MDD group are:Patients with MDDA MADRS score ≥ 7 and < 26 at screening

The main exclusion criteria for the MDD group are:Meeting diagnostic criteria for any major psychiatric disorder (other than MDD), as determined by SCID-5 at screeningHaving received fluoxetine within 90 days prior to visit 3Having received psychotherapy within 14 days prior to visit 3

The main inclusion criteria for the HV group are:Healthy

The main exclusion criteria for the HV group are:Meeting diagnostic criteria for any major psychiatric disorder, as determined by SCID-5 at screeningA lifetime history of psychiatric or neurologic disorders

### Recruitment of participants and informed consent

All study participants are recruited by the clinical research unit (Charité Research Organisation). It is anticipated that approximately six to eight subjects will be enrolled per month. The anticipated enrolment period is from June 2022 until September 2023.

Prior to performing any study-related procedure at screening, each potential subject must provide a signed and dated acknowledgement of their freely given informed consent (informed consent form (ICF)). Either the investigator or a designated person explains the aims, methods, anticipated benefits, and potential hazards of this protocol and any discomfort it may entail, and the subject is given an opportunity to discuss any questions regarding the trial procedures and conduction. The subject is allowed sufficient time to consider trial participation. The subject receives a signed copy of the ICF.

### Study discontinuation

Subjects can withdraw from the study at any time without consequences and without giving a reason. Subjects who choose to withdraw from the study or are withdrawn by the investigator (i.e., in case of adverse events or protocol violations) are defined as early study discontinuation. The date of discontinuation must be documented in the subject file and in the electronic case report form (eCRF) and sponsor and, if applicable (i.e., if the principal investigator (PI) is already aware of the dropout because of the PI being in direct contact with the subject, it is not needed to inform the PI in written form), the PI must be informed in written form by the study team. The PI can also discontinue the study if new safety concerns arise which are considered of relevant change to the benefit/risk assessment. The date of and the primary reason for the withdrawal, as well as the observations available at the time of withdrawal, are to be documented in the eCRF.

Reasons leading to the withdrawal of a subject can include the following (one primary reason must be determined):Intolerable adverse eventsStudy Stopping Rules (see next section)Lack of subject’s cooperation, e.g., subject’s request to withdraw, lack of complianceOther reasons (noting reason), e.g., important protocol deviations such as in/ex criteria not met but discovered only after randomization

In all subjects who finish the study prematurely, an early discontinuation examination, if possible, should be carried out.

### Study stopping rules

The study may be terminated at any time for any reason by the sponsor. The entire trial must be terminated prematurely including, but not limited to, the following reasons:The sponsor or the investigator considers that the number and/or severity of adverse events justify the discontinuation of the studyNew information is received regarding product safety or other issues arise related to the trial that precludes its completion (e.g., manufacturing issues such as unavailability of amisulpride or a placebo pill, insufficient overall recruitment of subjects, economic reasons such as the insufficient budget for the trial or insolvency of the sponsor or the Charité Research Organisation).

The reason for such a decision will be documented in writing. The respective independent ethics committee (IEC) and the applicable competent authority will be informed in writing as appropriate.

In case one, related (= causal relationship with the trial drug cannot be excluded) serious adverse events or repeated (≥ 2) severe related adverse events are reported, the trial will be interrupted, and no further treatments will be administered. The trial will only be restarted after a substantial amendment of the trial application has been submitted by the sponsor and a favorable opinion of the health authority and the ethics committee has been received. Subjects that already received treatment will be followed further to collect safety data until all adverse events possibly related to study participation or any study-associated procedure are followed up until they have resolved, have been sufficiently characterized or no further information can be obtained.

### Relevant concomitant care

During the screening period, prior and concomitant medications are recorded and reviewed throughout the study until visit 4. In particular, prescribed medication or psychotherapy as mentioned above are not permitted as concomitant treatments. Subjects who have taken prescription or non-prescription medication may still be entered into the study, if, in the opinion of the investigator, the medication does not interfere with the study procedures or compromise safety. Amisulpride will not be used in combination with medications which, e.g., could induce torsade de pointes (such as class Ia and class III antiarrhythmic agents), as well as other medications as indicated in the label of amisulpride.

If concomitant drugs are administered, these are recorded in the subjects’ file and eCRF. Permitted concomitant treatments are not to be changed during the course of this study.

Moreover, the following criteria concerning diet and lifestyle result in the withdrawal of the study subject:Consumption of large amounts of caffeinated drinks (more than 8 cups of standard caffeinated drinks (tea, instant coffee) or 6 cups of stronger coffee or other drinks containing methylxanthines such as Coca-Cola or Red Bull per dayConsumption of caffeinated drinks 2 h prior to the start of the fMRI scanSmoking/nicotine consumption 2 h prior to the start of the fMRI scanConsumption of food containing poppy seeds within 24 h prior to visits 3 and 4Consumption of alcohol within 24 h prior to visits 3 and 4.

As this study enrolls also women who are considered to be of childbearing potential, suitable measures must be taken to avoid falling pregnant. Male participants and female participants of childbearing potential must maintain highly effective contraception methods starting from the signing of the informed consent form and for at least 3 months after the last dose of study treatment. Men must agree to use condoms (including men who have had vasectomies) even if their partner is pregnant (this is to ensure that the fetus is not exposed to the study drug through vaginal absorption) and to not donate sperm and to not plan to father a child during the study and for 3 months after receiving the last dose of study drug. Male subjects must be counseled by the investigator that they should encourage their female partner to use a highly effective method of contraception consistent with local regulations regarding the use of contraceptive methods for subjects participating in clinical studies (e.g., prescription oral contraceptives, contraceptive injections, intrauterine device (IUD)) in addition to the condom used by the male study subject. Rescreening of withdrawn subjects is allowed once at the discretion of the investigator.

### Group randomization

After written informed consent is obtained, healthy and MDD subjects meeting all in-/exclusion criteria are randomized at baseline (visit 2) or visit 3 to receive either amisulpride or matching placebo.

Treatments are randomly allocated in a 1:1 ratio. Randomization is performed in accordance with prepared randomization lists provided by an independent vendor of the Charité Research Organisation. A qualified external pharmacy performs a patient/subject individual re-packaging of the study medication in capsule boxes in accordance with the unblinded randomization list. Each capsule box is labeled with the respective randomization number and contains the study medication (amisulpride or matching placebo). The label does not allow any inferences about the administered compound.

The randomization list is kept in safe and confidential custody. Only personnel not involved in study conduction has access to the list. Additionally, sealed emergency envelopes containing information on the subject’s trial medication are provided to the Charité Research Organisation.

Thereupon, the unblinded Study Team of the Charité Research Organisation receives one capsule box with the corresponding tablet (amisulpride or matching placebo) for each patient/subject per visit. The blinded investigator administers two single doses of the same blinded study medication (amisulpride or matching placebo) to each subject according to the respective randomization number.

Additional randomization numbers are used in case of replacements being needed. The investigator enrolls study participants and documents the randomization number in the eCRF.

### Pharmacological intervention

Amisulpride is an atypical antipsychotic of the benzamine class. It is a well-tolerated selective dopamine D2/3 receptor antagonist with high mesolimbic affinity [30, 31]. In Germany, amisulpride is approved for the treatment of positive and negative symptoms in acute and chronic schizophrenic disorders.

Amisulpride expresses dose-dependent effects as shown in preclinical research. At a high dose, amisulpride reduces dopaminergic neurotransmission at the postsynapses by antagonizing D2/D3 receptors. At a low dose, however, amisulpride has a higher affinity for presynaptic autoreceptors and thereby enhances dopamine signaling [30, 31]. In this study, two single low doses of amisulpride (100 mg) or matching placebo are administered. Since the aim of this study is to explore the the effects of modified dopaminergic signaling on reward circuits in the brain rather than the antidepressant effect of amisulpride, a placebo will be used in the control group instead of a standard antidepressant treatment.

Amisulpride is a commercially available product and the standard dose to treat negative symptoms in schizophrenia is 50–300 mg [31]. Hence, the administered dose in this study (100 mg) lies well within this range. Previous trials investigating the effects of low-dose amisulpride on reward- and motivation-related processing using fMRI reported no serious adverse events [29, 33, 35]. Amisulpride is well tolerated at low doses and has no clinically significant effects on memory and psychomotor performance [31, 45].

In this study, amisulpride and matching placebo are administered orally in the form of a white tablet under fasted conditions 3.5 to 4 h before the start of fMRI scanning at both Visit 3 and Visit 4 to ensure maximum plasma levels during the tasks. The placebo tablet was manufactured by Zentiva Pharma GmbH to resemble the amisulpride tablet. Medication is administered by the blinded site staff of the Charité Research Organisation. None of the investigators, neither the attending physician nor the study team of MSB Medical School Berlin know which treatment the respective subject received.

Plasma samples are collected to determine the blood levels of amisulpride. Blood samples are taken at pre-dose, and 1 h, 3.5 to 4 h, and 4.5 to 5 h after oral drug administration to determine pharmacokinetic parameters of amisulpride. Drug supplies are kept in their original packaging and in a secure limited access storage area according to the recommended storage conditions on the medication label. A temperature log is maintained for documentation. A standardized breakfast is served to subjects after administration of blinded study medication. Daytime of treatment is standardized across subjects. No drug dose changes will be performed.

### Strategies to improve adherence to interventions

All study participants receive medical monitoring and counseling during study participation. In addition, should they wish, participants are informed about the results of their task performance after the finalization of the study. By scheduling the study participants, it is guaranteed that the waiting time is short.

Study participants receive a financial remuneration, which covers all costs incurred by study participation. The financial remuneration is the same for HV and for MDD patients.

### Provisions for post-trial care

Adverse events are recorded at each site visit. Adverse events possibly related to study participation, or any study-associated procedure are followed up until they have resolved, have been sufficiently characterized or no further information can be obtained.

In the case that a study participant dies, or the body or health of the study participant is injured due to the participation in the clinical trial, there is an insurance policy in accordance with Sect. 40, paragraph 1, sentence 3, no. 8 of the German Medicines Act (AMG), which provides benefits even if no one else is liable for the damage.

### Endpoints

The primary endpoint of efficacy is:

- Blood-oxygenation-level-dependent (BOLD) fMRI parameter estimates (ß-weights within the generalized linear model (GLM) analysis) will be extracted from task-related regions of interest (ROI) (average %BOLD signal change and 90th percentile thereof within ROI) under the following task-specific contrastMID task:◦ Contrast of “high-gain” vs. “no-gain” condition during the task cue periodROI:◦ Ventral striatum (including nucleus accumbens)

Exploratory endpoints of efficacy are:

BOLD fMRI parameter estimates (ß-weights within the GLM analysis) will be extracted from task-related regions of interest (average %BOLD signal change and 90th percentile thereof within ROIs) under the following task-specific contrasts:SID task:◦ Contrast of “high-gain” vs. “no-gain” condition during the task CUE periodILT:◦ Contrast of the “gain-cue” vs. “neutral cue” conditions during the task cue and feedback periodsEBDM task:◦ Contrast of the “high reward” vs. “low reward” conditions during the task cue2 period◦ Contrast of the “high effort” vs. “low effort” conditions during the task Cue2 periodROIs for all tasks:◦ Ventral striatum (including nucleus accumbens), VTA, dorsal ACC, insula, vmPFC/OFC, and ventral pallidumReaction times and estimates of response accuracy extracted from the in-scanner protocol log filesBOLD fMRI signal magnitude and BOLD signal standard deviation during Resting State within the following a priori defined regions:◦ Default Mode Network (posterior cingulate, vmPFC, and medial temporal lobe), Central Executive Network (dorsolateral PFC, premotor cortex, precuneus), and Salience Network (amygdala, insula, and dorsal ACC)Increases in relative and absolute cerebral blood flow measured through arterial spin labeling MR in the whole brain and in the following brain regions:◦ (Bilateral): ventral striatum, vmPFC/PFC, VTA, dorsal ACC, insula, and ventral pallidum after amisulpride administration
◦ 
Changes in associations between the magnitude of BOLD signal during reward-and motivation-related processing, self-reported anhedonia, and behavioral measures after amisulpride administration as compared to placebo in MDD patients relative to HVChanges in associations between resting state functional connectivity, self-reported anhedonia, and behavioral measures after amisulpride administration as compared to placebo in MDD patients relative to HVChanges in plasma levels of amisulpride including correlation to changes in BOLD signal in MDD patients relative to HVChanges in whole brain BOLD signal after amisulpride administration as compared to placebo in MDD patients relative to HV

### Statistical analysis

All fMRI data (pre)processing and analysis are performed using FSL (Oxford, UK) according to custom practice and pipelines using the batch or Python programming languages. Additional data analyses are performed using SPSS software (IBM SPSS, New York, USA). Descriptive statistics (mean ± SD) are presented for all primary and exploratory outcomes. The statistical model to compare the primary and exploratory outcomes between the four groups MDD/placebo, MDD/amisulpride, HV/placebo, and HV/ amisulpride is an analysis of variance (ANOVA) including the main effects of treatment (amisulpride/placebo), group (MDD/HV) as well as interaction effects. Appropriate effect sizes (e.g., Cohen’s *d*) are reported. A detailed description of all statistical procedures for the fMRI analyses can be found in the statistical analysis plan in the appendix.

### Sample size

Power analysis for a one-way ANOVA with 4 groups was conducted in G*Power [46] to determine a sufficient sample size using a one-sided alpha of 0.05, a power of 0.95, and a large effect size (*d* = 0.84). Previous studies in HV and in patients with MDD found large effects (*d* > 0.8), showing a significant increase in striatal activity after amisulpride administration as compared to placebo in patients with MDD [32, 35]. The sample size needed with this effect size is *N* = 102 completers. In order to have the same number of subjects per group, we aim for 104 completers, i.e., 26 per group. Accounting for a drop-out rate of ∼15%, the estimated total sample size is *N* = 120 (30 subjects per group).

Screening for the trial will stop once a sufficient number of subjects has been measured and controlled for dropouts due to excessive head movement in the scanner and/or headaches and incomplete data.

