Most human studies investigated reward- and motivation-related processing in human experimental settings using monetary reward. However, as other entities like food or social interaction are intrinsically rewarding and therefore comparable according to preclinical research, variations of classical reward tasks also include social reward or food reward [22, 23].

Compared to healthy volunteers (HV), blunted activation in frontostriatal brain regions and poor behavioral responses during reward- and motivation-related decision-making were observed in MDD [24]. Several attempts have been made to investigate the effects of pharmacological intervention on reward- and motivation-related deficits in MDD [25–29]. However, mixed effects have been reported in this context and neurobiological mechanisms underlying deficits in reward- and motivation-related processing are still unclear.

A promising option to investigate treatment effects on reward- and motivation-related deficits is to specifically target dopaminergic neurotransmission in frontostriatal brain regions by using pharmacological interventions that are specific for and have high affinity to dopamine receptors such as amisulpride [25, 29]. Amisulpride’s pharmacological efficacy relates to its high mesolimbic affinity and its properties as a selective dopamine D2/D3 receptor antagonist at the postsynapses at high doses (400–1200 mg per day) [30, 31]. At a low dose (50–300 mg per day), amisulpride has a higher affinity to block presynaptic autoreceptors and thereby increases dopaminergic signaling at the synapse [31].

Amisulpride reduced striatal activation and worsened behavioral performance during an instrumental learning task in HV at a high single dose (400 mg) [32], while at a single lower dose (200 mg) it improved reward learning and enhanced striatal activation during the task [33]. During reward anticipation as assessed using the MID task; however, no effect of a single low dose (200 mg) of amisulpride was observed, which could possibly be due to ceiling effects in healthy subjects [34]. In MDD, associated with dopamine deficiency, single low-dose amisulpride (50 mg) enhanced striatal activations and enhanced connectivity between the ventral striatum and midcingulate cortex during the MID task compared to HV, but did not impact impaired reward learning in MDD patients [29, 35]. The effects of amisulpride on reward valuation in MDD have not been investigated yet.

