## Methods

### Study design

This single-center, double-blind, placebo-controlled, randomized, single-dose, parallel-group study is designed to investigate the effects of a single dose of amisulpride on functional brain changes during reward- and motivation-related processing and at rest. The study is conducted by the Charité Research Organisation, a contract research organization and subsidiary of the Charité – Universitätsmedizin Berlin. A total of 120 participants will be recruited. Measurement of functional brain changes is performed after a single dose of amisulpride or placebo in HV and patients with MDD.

It is hypothesized that functional brain changes previously linked to reward- and motivation-related processing require dopaminergic signaling and are diminished in MDD compared to HV. In MDD, but not in HV, the administration of a single low dose (100 mg) of amisulpride should increase brain activation associated with reward- and motivation-related processing.

MDD patients (*n* = 60) and HV (*n* = 60) are randomly allocated in a 1:1 ratio to the two treatment arms (MDD/amisulpride *n* = 30, MDD/placebo *n* = 30, HV/amisulpride *n* = 30, HV/placebo *n* = 30). The effects of a single dose of amisulpride (100 mg) on functional brain changes are assessed during reward- and motivation-related processing and at rest.

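### The stated 95% power belongs to a four-group omnibus F test; at the same effect size the tests of the drug hypothesis in the planned 2×2 model have about 56% (interaction) and 85% (drug effect within MDD)

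*Protocol article*

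**What the plan says.** The Sample size section describes the calculation as follows: "Power analysis for a one-way ANOVA with 4 groups was conducted in" G*Power, "using a one-sided alpha of 0.05, a power of 0.95, and a large effect size" of d = 0.84. It arrives at 102 completers, rounds to 104 (26 per group), and enrols 120 (30 per group) to allow for dropout. It supports the effect size by references 32 and 35, described as "showing a significant increase in striatal activity after amisulpride administration as compared to placebo in patients with MDD".

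The Statistical analysis section plans something different: an ANOVA "including the main effects of treatment (amisulpride/placebo), group (MDD/HV) as well as interaction effects".

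The Study design section gives two hypotheses. One is that reward-related activation is lower in MDD than in HV. The other concerns the drug: "In MDD, but not in HV, the administration of a single low dose" should raise activation.

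The Background and rationale section describes reference 32 in these words: "Amisulpride reduced striatal activation and worsened behavioral performance during an instrumental learning task in HV at a high single dose" of 400 mg.

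**The concern.** A one-way ANOVA over four groups asks whether any of the four means differ. It does not separate a drug effect from a difference between patients and volunteers, and the protocol expects such a difference. The drug hypothesis is answered by 1-df tests in the 2×2 model: the treatment-by-group interaction and the amisulpride-versus-placebo contrast within MDD. The article gives no power for either, so the only power figure in the document attaches to a test that does not address the drug hypothesis.

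What is at stake is how a null result is read. A reader who carries the 95% over to the interaction would take a non-significant result as strong evidence against a selective effect, although the chance of detecting the assumed effect was little better than even.

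The support for the effect size has a separate flaw. A study that the article itself describes as finding reduced striatal activation is cited for an increase.

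**Working it through.** **Inputs.** From Sample size: four groups, alpha 0.05, power 0.95, d = 0.84, 102 completers needed, 104 planned (26 per group), 120 enrolled. From Study design: a drug effect in MDD and none in HV. From Statistical analysis: a 2×2 model with interaction. All effects below are in SD units with a common SD.

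**Step 1. Reproduce the plan's figure.** Convert d to Cohen's f by f = d/2 = 0.84/2 = 0.42. The omnibus F test has df1 = 3, df2 = N − 4 and noncentrality N·f².
- N = 101: power 0.949
- N = 102: noncentrality 102 × 0.1764 = 17.99, power 0.951
- N = 104: noncentrality 104 × 0.1764 = 18.35, power 0.955

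So 102 is the smallest N reaching 0.95. Alternatives do not give 102: a 1-df test with f = 0.42 gives 76, alpha 0.10 gives 86, and f = 0.40 gives 112.

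**Step 2. Which patterns have f = 0.42?** With equal groups, f is the standard deviation of the four means. For means 0, 0 (HV) and 0.84, 0.84 (MDD; the sign is immaterial), the grand mean is 0.42 and every deviation is 0.42, so f = 0.42. A pure patient-versus-volunteer difference with no drug effect therefore gives the omnibus test 95.5% power at 104.

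**Step 3. The hypothesised drug pattern under the omnibus test.** Let one cell (MDD/amisulpride) differ by 0.84 from three equal cells. The grand mean is 0.21 and f² = (3 × 0.21² + 0.63²)/4 = 0.1323, so f = 0.364. Noncentrality is 104 × 0.1323 = 13.76 and power is 0.877. The value is the same if MDD/placebo is the one cell that differs, that is, a deficit of 0.84 fully restored by the drug.

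**Step 4. Interaction, 26 per group.** The contrast is (MDD drug effect) − (HV drug effect) = 0.84 − 0 = 0.84. Its SE is √(4/26) = 0.392, so the noncentrality is 0.84/0.392 = 2.142 on 100 df. Power is 0.564 two-sided and 0.685 one-sided at 5%.

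**Step 5. Drug effect within MDD, 26 versus 26.** The SE is √(2/26) = 0.277, so the noncentrality is 0.84/0.277 = 3.029. With the pooled error of the four-group model (100 df), power is 0.851 two-sided and 0.914 one-sided. Using MDD patients only (50 df), it is 0.844 and 0.910.

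**Step 6. Sensitivity.**

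| Assumption | Interaction | Drug effect within MDD |
|---|---|---|
| d = 0.84, 26 per group, two-sided | 56% | 85% |
| d = 0.84, 26 per group, one-sided | 69% | 91% |
| d = 0.84, all 120 complete, two-sided | 63% | 90% |
| d = 0.84, all 120 complete, one-sided | 74% | 94% |
| d = 0.5, 26 per group, two-sided | 24% | 43% |

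For d = 0.5 the noncentralities are 0.5/0.392 = 1.275 and 0.5/0.277 = 1.803. The MDD column uses the pooled error.

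**Step 7. The cited support.** Sample size cites reference 32, alongside 35, for an increase after amisulpride. Background and rationale describes reference 32 as a 400 mg study in HV in which striatal activation fell. The direction is opposite, and the dose is one the article itself classes as high.

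**The case against.** The strongest reply is that the article attaches 95% openly to a one-way ANOVA, that the arithmetic is right, and that an MDD-versus-HV difference is itself one of the two hypotheses, so an omnibus test sensitive to it is not irrelevant. That is fair, and the finding is not an arithmetic error. What remains is that one omnibus test cannot tell the two hypotheses apart, while the effect size it uses comes from a drug effect in patients.

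A second reply is that f = 0.42 might be meant for the interaction itself. Power would then be about 99%, but this needs a difference between drug effects of 4 × 0.42 = 1.68 SD, twice the cited d.

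Several stronger readings are tempting but not supported:
- That the trial has only 56% power for its question. No single primary test is named, and 56% is the figure for one candidate under one set of assumptions; the MDD contrast has about 85%.
- That selectivity will be claimed from a significant result in MDD beside a non-significant one in HV. The article proposes no such inference and already has the interaction in its model. Test hierarchy and rules for claims may properly sit in the analysis plan, which is not shown.
- That the one-sided wording distorts N. An F test rejects in the upper tail, and 0.05 there is what yields 102. The wording is loose for an F test and matters only once 1-df tests are reported.
- That the reported absence of an effect at 200 mg in HV contradicts the plan. It agrees with expecting no effect in HV.
- That 120 is too few for 104 completers. A loss of 16 out of 120 is 13.3%, within the approximate 15% given.

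On the citation, the sentence refers to studies in HV and in MDD, so reference 32 may be meant as the HV study. Its direction still does not support an increase.

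**Conclusion.** The concern holds in this form: the 95% is correct for the omnibus test with f = 0.42 and does not carry over to the tests of the drug hypothesis in the planned model. Under d = 0.84 in MDD, no effect in HV and 26 completers per group, neither 1-df test reaches 95%, whether one- or two-sided, and neither does so even if all 120 participants complete. The omnibus figure of 88% further assumes that the other three cells are equal; a larger patient-volunteer difference would raise it without helping either drug test. An effect in HV in the same direction would lower the interaction power further. For scale, 95% power for the two-sided interaction under these assumptions would take 297 completers. That shows the size of the gap and is not a call to enlarge the trial.

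**What to change.** Keep N = 120. In Sample size, replace the 95% omnibus claim with the power of the tests in the planned 2×2 model: amisulpride versus placebo within MDD, and the treatment-by-group interaction. State the assumptions (26 completers per group, d in MDD, zero in HV) and whether alpha is one- or two-sided for these 1-df tests. On a two-sided 5% basis the figures are about 85% and 56% for d = 0.84, and about 43% and 24% for d = 0.5. Remove reference 32 as support for an increase in striatal activity. Which of the two tests leads, and how claims are ordered, is for the sponsor and the analysis plan to settle.

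The cost is a rewording of one section and a less favourable stated power. No additional participants are needed and no study procedure changes.
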